#### Dietary and Lifestyle Advice

Healthy dietary and lifestyle advice is individually tailored to create a mild energy deficit and gentle increase in activity. This advice is given by appropriately trained healthcare professionals. It is usual practice and considered very safe. In the unlikely event of side effects participants may contact the trial team to discuss any concerns. To this end, all participants are given a credit card-sized card with the trial team's contact details on that will allow participants to report perceived serious adverse effects and receive advice as required.

#### NRT Patches

NRT has been investigated in several hundred previous clinical trials and is widely prescribed worldwide and subject to safety monitoring, and is replacing a product, nicotine, which the participants are already consuming and will have consumed for many years in cigarettes. Thus, there is every reason to expect that treatment in this trial is safe. Participants are warned about the side-effects of NRT and advised not to stop taking the medication without consulting with the trial team or an NHS professional if the trial team are unavailable. Participants will record the occurrence of side-effects of medication as specified on the summary of product characteristics (SPC) for all relevant NRT preparations, by completing a checklist. The checklist is given to the trial healthcare professional and the healthcare professional will enquire about recorded adverse events, so as to determine the severity of any adverse event and ensure that appropriate advice is given for its management (such as rotating the patch site or use of emollients for skin reactions). Minor adverse reactions are monitored and managed in this way. For each known side effect listed in the SPC, the trial healthcare professional will have a definition of clinical severity. For example, a mild skin site reaction to the patch is defined as burning sensation that does not interfere with normal activities, redness or swelling at the site of application, or mild blistering. Any reaction beyond that is classified as potentially moderate or severe and is reported to and discussed with the principal investigator. A decision on stopping therapy will then be made with the participant, attending clinician, principal investigator, and other relevant parties as appropriate. Nicotine has a short half life (2 hours), meaning that the blood concentration will not build up during the course of treatment so that new side-effects are not expected after the first few weeks. In addition, reactions to it relate to local use, such as skin discomfort from patches and people become accustomed to the side-effects after a short time of using the preparation. The advice given will depend upon the severity of the reported reaction and those with moderate reactions are invited to an ad hoc consultation.

The SPCs for the relevant NRT products contain no warnings about serious adverse reactions except rare allergic reactions, such as angioedema, and cardiac arrhythmias, occurring in less than 1/1000 users. Thus we expect no or very few SUSARs (suspected unexpected serious adverse reaction) in this trial. The long history of use in and outside of trials for NRT means that SUSARs are unlikely. On the reverse of the trial card given the contact number for advice on side-effect management, there are instructions for reporting of serious adverse events. Through direct contact from the participant or contact from their attending physician, we expect to become aware of serious adverse events. If any member of the trial team becomes aware, they will inform the principal investigator within 24 hours. The principal investigator will then assess the seriousness, causality, expectedness and severity of the adverse effects. An immediate decision is made on the interim use of medication for that participant. If an event is judged severe, it is reported to the trial sponsor, who will report the event to the REC. Definitions of adverse events are contained in additional file 3.

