#### Salbutamol

Salbutamol has been thoroughly investigated in clinical trials and is widely prescribed worldwide and subject to safety monitoring. Thus, there is every reason to expect that its use in this trial is safe. Common side effects to salbutamol are mild (e.g. headache, tremor) and rare with small doses; severe reaction is very rare. Any reaction tends to be immediate. Participants are warned about the side-effects of salbutamol and asked to give verbal consent to taking it. They will take a small dose (200 mcg) in the company of healthcare professionals and given a contact number should they experience any adverse events in the hours that follow. This is administered 4 times during the year, at baseline, 12 weeks, 6months and 1 year. For each known side effect listed in the SPC, the trial healthcare professional will have a definition of clinical severity. Any reaction beyond that is classified as potentially moderate or severe and is reported to and discussed with the principal investigator. If it is felt that a person has suffered side-effects which are related to the salbutamol then they will not have the salbutamol administered next time.

The long history of use in and outside of trials for salbutamol means that SUSARs are unlikely. On the reverse of the trial card given the contact number for advice on side-effect management, there are instructions for the reporting of serious adverse events. Through direct contact from the participant or contact from their attending physician, we expect to become aware of serious adverse events. If any member of the trial team becomes aware, they will inform the principal investigator within 24 hours. The principal investigator will then assess the seriousness, causality, expectedness and severity of the adverse effects. If an event is judged severe, it is reported to the trial sponsor, who will report the event to the Research Ethics Committee (REC). Definitions of adverse events are contained in additional file 3.

Participants are asked weekly to report intercurrent illnesses and the response recorded. If any of these intercurrent illnesses contra-indicates Salbutamol, NRT, VLCD or Healthy Dietary Advice, this is immediately reported to the principal investigator and a decision made about continued use.

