### Ethics and Research Governance

The trial is conducted in compliance with the principles of the Declaration of Helsinki (1996), the principles of the International Conference on Harmonisation (ICH)-Good Clinical Practice (GCP) and run in accord with EU Clinical Trials Directive and all of the applicable regulatory requirements. The study protocol and other documentation have been approved by South Birmingham Research Ethics Committee, Birmingham and Black Country Comprehensive Local Research Network and West Midlands South Comprehensive Local Research Network. Any subsequent protocol amendments will be submitted to the REC for approval and the other bodies if necessary. We will comply with ICH-GCP Guidelines over the reporting of adverse events (AEs), serious adverse events (SAEs) and suspected unexpected serious adverse reaction SUSARs. In addition we will provide the REC with progress reports as well as a copy of the final study report.

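### The step that sends events to the sponsor and ethics committee turns on severity, not seriousness, so a serious event of mild or moderate intensity has no explicit route to them

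*Protocol article*

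**What the plan says.** All of this is in the protocol article.

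- **NRT Patches, start of the pathway.** The trial card carries instructions for reporting serious adverse events, and the team expects to hear of them from the participant or the attending physician. Then: "If any member of the trial team becomes aware, they will inform the principal investigator within 24 hours".
- **NRT Patches, assessment.** "The principal investigator will then assess the seriousness, causality, expectedness and severity of the adverse effects".
- **NRT Patches, onward step.** "If an event is judged severe, it is reported to the trial sponsor, who will report the event to the REC".
- **Salbutamol.** The same sequence is set out again, with the same condition for going to the sponsor and REC.
- **NRT Patches, severity as a grade.** A mild patch-site reaction is defined, followed by: "Any reaction beyond that is classified as potentially moderate or severe and is reported to and discussed with the principal investigator".
- **VLCDs and Dietary and Lifestyle Advice.** Moderate or severe VLCD side effects go to the principal investigator. Participants carry a contact card for serious effects. Neither part describes a step to the sponsor.
- **Ethics and Research Governance.** "We will comply with ICH-GCP Guidelines over the reporting of adverse events (AEs), serious adverse events (SAEs) and suspected unexpected serious adverse reaction SUSARs".

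Both the NRT and the salbutamol text refer to additional file 3, which is not shown, for the definitions of adverse events.

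**The concern.** The pathway begins with serious adverse events and ends with a condition on a different attribute. Seriousness and severity are not interchangeable here, because the article asks the principal investigator to judge each of them. Read literally, seriousness, causality and expectedness are all assessed, but none of them decides whether the sponsor and REC are told.

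What is at stake is oversight. The sponsor and REC rely on this step to see serious events while the trial is running. Staff who follow the specific instruction could hold back an event that the governance section promises to report, and each could point to the document in support.

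**Working it through.** No arithmetic decides this point. The check sets the statements side by side and applies them to each type of event.

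**1. Does *severe* mean *serious* in this article?** The assessment sentence lists seriousness and severity as two of four attributes. The side-effect text uses mild, moderate and severe as an intensity scale. In the article's own vocabulary, *judged severe* is therefore a grade of intensity.

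**2. What does the governance commitment select on?** It names AEs, SAEs and SUSARs. The S for serious is part of both SAE and SUSAR, and the NRT Patches text spells out SUSAR as a suspected unexpected serious reaction. Expedited attention therefore follows seriousness and, for SUSARs, expectedness and suspicion of a causal link. Intensity plays no part.

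**3. Apply both statements.**

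| Event | Principal investigator told? | Meets the stated condition for sponsor and REC? | SAE under the governance commitment? |
|---|---|---|---|
| Serious and severe | Yes, within 24 hours | Yes | Yes |
| Serious, mild or moderate | Yes, within 24 hours | No | Yes |
| Severe, not serious | Yes, by the side-effect route | Wording met, but entry to this sequence not shown | No |
| Neither | Only if graded moderate | No | No |

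The second row is the gap. The NRT text itself names angioedema and cardiac arrhythmias as rare serious reactions. Their intensity would be a separate judgement, so either could fall in that row.

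**4. Is there another stated route to the sponsor?** None appears in the VLCDs, Dietary and Lifestyle Advice, NRT Patches or Salbutamol parts. The only described step is the one conditioned on severity.

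**5. Is it a slip in one place?** No. The condition is written twice, once for NRT and once for salbutamol.

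**6. Can the gap be sized?** Only in part. The one frequency given is for the named NRT reactions, at fewer than 1 in 1000 users. With the recruitment aim of 42 per group, 3 × 42 = 126 participants, and 126 × 1/1000 = 0.126. A reaction at that frequency would thus be expected fewer than 0.126 times in the trial. The figure says nothing about serious events from other causes, about events on the diets, or about how serious events divide by intensity.

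**The case against.** The best defence is context. In both places the sentences leading up to the rule are about serious adverse events, so *judged severe* may be loose wording for *confirmed as serious*. That is plausible as intent. The sentence immediately before it separates the two terms, however, so a nurse or investigator cannot be expected to read one as the other.

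A second defence is that an article condenses a fuller clinical protocol, and that additional file 3 may settle the matter. The file is cited for definitions, not for a reporting trigger. If it keeps the terms apart, the conflict remains. If it equates them, it conflicts with their separate listing. In any case the point is not an omission, because the article states a rule and states it twice.

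Several stronger readings are tempting and are not supported:

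- A reader might infer that events are reported *only if* severe, and that every serious but non-severe event is lost. The text says if. The principal investigator is still informed and still assesses seriousness, and the governance commitment may prompt a report.
- A reader might infer that an intense but harmless headache would be sent to the sponsor. Ordinary side effects have their own checklist route, and nothing shows that such an event would enter the serious-event sequence.
- A reader might infer particular harm for VLCD users with a BMI of 25 to 30 or on thiazides. The faulty condition stands in the NRT and salbutamol text and not in the VLCD text.
- A reader might infer that the safety record for the later trial would under-count serious events. The rule governs onward notification, not recording.

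**Conclusion.** The point holds as a conflict between a specific instruction and a general commitment. The trigger named in the NRT Patches and Salbutamol parts is the wrong attribute for a serious-event pathway and does not match Ethics and Research Governance. Serious events of mild or moderate intensity are left without an explicit route to the sponsor or REC, and *could* go unreported to them. The documents do not establish that they *would*.

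The conclusion rests on two assumptions: that *severe* carries the intensity meaning used in the rest of the safety section, and that no other written route to the sponsor exists beyond the article. No estimate or analysis in the trial depends on it. It is worth correcting because it touches safety oversight and the remedy is small.

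**What to change.** In NRT Patches and in Salbutamol, make the condition for reporting to the sponsor and REC that the event is judged *serious*, so that it agrees with Ethics and Research Governance. Keep severity as a recorded grade alongside causality and expectedness.

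Add one sentence saying that the same route applies to serious events in all three arms, whether or not the event is attributed to the patch or to salbutamol. All participants receive patches, so this may already be intended, but the VLCD and dietary advice parts describe no step to the sponsor.

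Check that additional file 3 and the site procedures use the two terms in the same way. The cost is one word in two places, one added sentence and the matching site instruction. Sample size, treatment, visit schedule and analysis are unaffected.

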#### Salbutamol

Salbutamol has been thoroughly investigated in clinical trials and is widely prescribed worldwide and subject to safety monitoring. Thus, there is every reason to expect that its use in this trial is safe. Common side effects to salbutamol are mild (e.g. headache, tremor) and rare with small doses; severe reaction is very rare. Any reaction tends to be immediate. Participants are warned about the side-effects of salbutamol and asked to give verbal consent to taking it. They will take a small dose (200 mcg) in the company of healthcare professionals and given a contact number should they experience any adverse events in the hours that follow. This is administered 4 times during the year, at baseline, 12 weeks, 6months and 1 year. For each known side effect listed in the SPC, the trial healthcare professional will have a definition of clinical severity. Any reaction beyond that is classified as potentially moderate or severe and is reported to and discussed with the principal investigator. If it is felt that a person has suffered side-effects which are related to the salbutamol then they will not have the salbutamol administered next time.

The long history of use in and outside of trials for salbutamol means that SUSARs are unlikely. On the reverse of the trial card given the contact number for advice on side-effect management, there are instructions for the reporting of serious adverse events. Through direct contact from the participant or contact from their attending physician, we expect to become aware of serious adverse events. If any member of the trial team becomes aware, they will inform the principal investigator within 24 hours. The principal investigator will then assess the seriousness, causality, expectedness and severity of the adverse effects. If an event is judged severe, it is reported to the trial sponsor, who will report the event to the Research Ethics Committee (REC). Definitions of adverse events are contained in additional file 3.

Participants are asked weekly to report intercurrent illnesses and the response recorded. If any of these intercurrent illnesses contra-indicates Salbutamol, NRT, VLCD or Healthy Dietary Advice, this is immediately reported to the principal investigator and a decision made about continued use.

### Ethics and Research Governance

The trial is conducted in compliance with the principles of the Declaration of Helsinki (1996), the principles of the International Conference on Harmonisation (ICH)-Good Clinical Practice (GCP) and run in accord with EU Clinical Trials Directive and all of the applicable regulatory requirements. The study protocol and other documentation have been approved by South Birmingham Research Ethics Committee, Birmingham and Black Country Comprehensive Local Research Network and West Midlands South Comprehensive Local Research Network. Any subsequent protocol amendments will be submitted to the REC for approval and the other bodies if necessary. We will comply with ICH-GCP Guidelines over the reporting of adverse events (AEs), serious adverse events (SAEs) and suspected unexpected serious adverse reaction SUSARs. In addition we will provide the REC with progress reports as well as a copy of the final study report.

### Data management, protection and confidentiality

The trial is being run as part of the portfolio of trials in the Primary Care Clinical Research and Trials Unit (PCCRTU), NIHR accredited trials unit number 33, in Primary Care Clinical Sciences at the University of Birmingham. The data management is run in accord with the standard operating procedures (SOPs), which are fully compliant with the Data Protection Act and ICH GCP. The trial registered with the Data Protection Act website at the University of Birmingham. Patient identifiable data is shared only within the clinical team on a need-to-know basis to provide clinical care and ensure good and appropriate follow up. Patient identifiable data will also be shared with the GP and approved auditors from the REC or NHS Research & Development (R&D) will also be able to see patient identifiable information. Otherwise, confidentiality is maintained and no one outside the trial team will have access to either the case report forms (CRFs) or the database. The source documents for the trial are CRFs which are stored in a locked cabinet at the participating practice. The trial database is securely held and maintained by the PCCRTU. On completion of the trial and data checking, the CRFs are transferred to Modern Records, a secure archiving facility at the University of Birmingham, where they are held for 15 years and then destroyed. The database is anonymised and a secure CD containing the link between ID number and patient identifiable information is stored in modern records.

### Publication

The trial results will be written up for submission to a peer reviewed journal and the trial is registered with ISRCTN. No data relating to individuals will be identified in these publications.
